## Abstract

**Background:**

Abused and neglected children are at increased risk of health problems throughout life, but negative effects may be ameliorated by nurturing family care. It is not known whether it is better to place these children permanently with substitute (foster or adoptive) families or to attempt to reform their birth families.

Previously, we conducted a feasibility randomised controlled trial (RCT) of the New Orleans Intervention Model (NIM) for children aged 0–60 months coming into foster care in Glasgow. NIM is delivered by a multidisciplinary health and social care team and offers families, whose child has been taken into foster care, a structured assessment of family relationships followed by a trial of treatment aiming to improve family functioning. A recommendation is then made for the child to return home or for adoption.

In the feasibility RCT, families were willing to be randomised to NIM or optimised social work services as usual and equipoise was maintained. Here we present the protocol of a substantive RCT of NIM including a new London site.

**Methods:**

The study is a multi-site, pragmatic, single-blind, parallel group, cluster randomised controlled superiority trial with an allocation ratio of 1:1. We plan to recruit approximately 390 families across the sites, including those recruited in our feasibility RCT. They will be randomly allocated to NIM or optimised services as usual and followed up to 2.5 years post-randomisation. The principal outcome measure will be child mental health, and secondary outcomes will be child quality of life, the time taken for the child to be placed in permanent care (rehabilitation home or adoption) and the quality of the relationship with the primary caregiver.

**Discussion:**

The study is novel in that infant mental health professionals rarely have a role in judicial decisions about children’s care placements, and RCTs are rare in the judicial context. The trial will allow us to determine whether NIM is clinically and cost-effective in the UK and findings may have important implications for the use of mental health assessment and treatment as part of the decision-making about children in the care system.

## Administrative information

Note: the numbers in curly brackets in this protocol refer to SPIRIT checklist item numbers. The order of the items has been modified to group similar items (see http://www.equator-network.org/reporting-guidelines/spirit-2013-statement-defining-standard-protocol-items-for-clinical-trials/).

## Introduction

### Background and rationale {6a}

Children who experience maltreatment in early life are at increased risk of a range of adverse mental and physical health outcomes including substance misuse, cardiovascular disease [1], self-harm, suicide attempts and suicide [2–5]. Early childhood adversity and associated disorders impose a massive financial burden on individuals, families and society [6]. Maltreated young people are overrepresented in inpatient psychiatric units, although they can benefit from intensive community care services [7]. Maltreatment-associated mental health problems, e.g. conduct disorder and attention deficit hyperactivity disorder (ADHD), are treatable [8, 9], so improving the mental health of young maltreated children is likely to yield substantial rewards in terms of the health and productivity of individuals, families and the population as a whole [10].

For maltreated children, the most important intervention may be the provision of a safer and more nurturing home environment: research on sensitive periods in neural development suggests that addressing inadequate care in the early months and years of life may improve neural circuits underpinning social development [11] and allow maltreated children to reach their full developmental potential [12]. More than 57,000 children were in foster care in England in March 2020 and, in June 2019, 4800 children were in foster care in Scotland [13]—around 4 to 5 in every 1000 children [14, 15]. Recovery from the effects of early maltreatment can be rapid if safe nurturing care is achieved early enough, ideally in the first year of life [16], whereas robust predictors of poor outcome for maltreated children include prolonged pre-care exposure to multiple adversities, placement instability and “drift” in care [17]. Despite this knowledge, nearly a third of infants (31%) and nearly a quarter of children aged 1–4 years (24.5%) will return to foster care within 5 years of being reunited with their parents [18]. There is much current debate about the ethics of permanent care (i.e. adoption) for maltreated children [19, 20] and the timescales involved in making these decisions [21]. In the UK, adoption does not take place on average until at least 3 years of age [21] despite the presence of adversity in most cases since birth. There are currently no evidence-based interventions aiding social work services and the legal profession to make the difficult decision about whether a pre-school child in care should be adopted or returned home.

Because of the poor health outcomes for maltreated infants in our current system, new technologies should be tested that have the potential to provide safe, nurturing care in timescales that allow benefits in terms of optimal brain development. The most effective way to improve the mental health of young children is to target *both* child behaviour problems *and* parent-child relationships, and medium to large effect sizes on a range of outcomes have been noted with these strategies [22, 23]. Although there is evidence that specialised foster care can be cost-effective for young children requiring substitute care [24], there is a lack of focus on placement outcomes [23] and we are not aware of any previous or current randomised controlled trials (RCTs) addressing decisions about whether children should be adopted or returned home. The aim of the Best Services Trial is to provide evidence to inform future service developments and policy decisions about the most effective and cost-effective approach for assessment of and intervention for children entering foster care due to abuse and neglect. Our primary outcome is child mental health. We hypothesise that introducing the New Orleans Intervention Model (NIM) into care proceedings for maltreated pre-school children coming into care will be a clinical and cost-effective way of improving their mental health.

## Feasibility trial

A detailed feasibility trial (NCT01485510), funded by the Chief Scientist Office (CSO) for Scotland (December 2011–May 2015) then by UK children’s charity NSPCC (nspcc.org.uk) (June 2015 to December 2015), was conducted to determine whether a definitive multicentre UK RCT was feasible, acceptable and necessary, what the required size of a definitive RCT would need to be and to ascertain the optimal outcome measures for a definitive trial. The funding for the definitive trial commenced in January 2016, and a protocol for the definitive trial was published in 2017 [25], although methodological challenges experienced in the London site meant that the multi-site definitive trial did not begin until Autumn of 2017. Due to this delay, and then further delays due to COVID-19, a funding extension was sought and granted. Once it became clear, in early 2021, that the definitive trial would be achievable, a more detailed protocol paper was warranted to describe the various challenges and contextual changes that necessitated the methodological variations we describe below.

The timelines of the feasibility and definitive trials are as follows in Table 1.

**Table 1 Tab1:** Timelines of stages of Best Services Trial

Stage	Feasibility RCT CSO funded	Bridging period NSPCC funded	NIHR funding/legal challenge to London randomisation	Definitive RCT with London site	End of recruitment	New end date with 2.5-year follow-up
Time	Dec 2011–May 2015	June 2015–Dec 2015	Jan 2015–28.08.2017	29.08.2017	31.7.21	29.02.2024
Randomisation condition	Consent > baseline > randomisation	Randomisation > consent > baseline		Consent > randomisation > baseline		
Key challenges	Very high recruitment rate and delays to accessing services	Waiting lists due to teams treating non-RCT families		Potential for bias to be introduced through post-randomisation baseline assessment—necessary to comply with judicial requirements		

These have included the following:
A very high initial response rate during the feasibility trial caused us to carefully examine the ethics of consent in the target population. In order to try to improve the ethical basis for the study, we introduced randomisation before consent (modified Zelen randomisation [26]). Unanticipated consequences of randomisation before consent included delays in service delivery since the infant mental health teams, which had had their capacity modelled on likely trial recruitment numbers, became overwhelmed with treating non-trial participants who were randomised but did not then consent to the study.A judicial challenge to randomisation in London required us to carefully examine randomisation procedures to ensure they complied with both the NHS governance framework and the judicial framework. Although our randomisation-before-consent procedure had been instituted in an attempt to improve the ethical basis for the study, we realised that, on balance, it had raised additional ethical problems: families randomised to NIM were having to wait for the intervention for study-related reasons which was potentially detrimental [12]. Because of the very short timescales available for parenting capacity assessments imposed on English care proceedings by the English Family Justice Review [27], it was crucial that interventions could begin immediately after the child was placed in care, so we instituted a new system of randomisation after consent, but prior to baseline assessment.A reduction in numbers of children coming into foster care and a parallel increase in the use of kinship care placements in Glasgow led us to include children coming into an episode of kinship care where the local authority placed statutory governance around the placement. Permanence procedures for kinship placements had been amended, and it was determined that there would be sufficient oversight of such placements for them to have the same stability and safety as foster care placements and thus would be appropriate to be randomised to receive NIM or Case Management.

## Objectives {7}

The main objective of the trial is to establish if NIM is more effective in improving the mental health of maltreated infants and young children than services as usual (SAU), i.e. social work Case Management (CM) [28].

There are 3 secondary objectives: compared to social work Case Management SAU, to establish whether NIM is effective in improving the relationship between maltreated infants and young children and their primary caregiver, whether NIM effects more timely permanent placement decisions for maltreated children at 2.5 years post-randomisation and whether NIM is cost-effective in terms of the short-term mental health of the child and in terms of a long-term population health model.

## Trial design {8}

A multi-site, pragmatic, single-blind, parallel group, cluster randomised controlled superiority trial with an allocation ratio of 1:1.

## Methods: participants, interventions and outcomes

### Study setting {9}

The study settings are social services in the local authorities feeding into the two trial sites: Greater Glasgow and Clyde (Scotland) comprising Glasgow City Council and, from October 2018, Renfrewshire Council; and London (England), including 6 boroughs Croydon, Tower Hamlets, Sutton, Bromley, Newham and Barking and Dagenham. Although each site is in the UK, the social services and legal contexts in each differ considerably.

### Eligibility criteria {10}

#### Inclusion

Families are eligible for the trial if they have a child aged 0 to 60 months who enters care in the recruiting sites for reasons associated with maltreatment, during the study recruitment period. Participants are included in the trial upon completion of written informed consent from the birth family and the child’s foster or kinship family.

In the event of a subsequent child being taken into care among participating families, consent will be sought from parent(s) and carers to include the new child. If consented, the new child will not be randomised, but will instead be allocated to the same arm of trial as their previous family members. This is partly to avoid contamination, but also because the aim of NIM is to help the parent(s) become more nurturing for both the current and any future children, and if a parent has already had NIM, it might be confusing for them to receive an intervention with a different and potentially contradictory ethos.

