We have found only one intervention, NIM, that uses an infant mental health approach aiming to improve the quality of permanent placement decisions so that children can experience appropriate nurturing care as early in life as possible [34]. The Tulane Infant Team, who developed NIM, assesses the mental health and relationship quality of every maltreated child under 5 years of age on reception into care. A tailored intervention is then offered to each family aiming to improve parent-child relationships and child mental health. These assessments and the degree of change achieved through intervention inform recommendations to the legal system about the permanent future care of the child. Where significant change has been achieved, it is recommended that children are rehabilitated back to the birth family. If not, the recommendation is adoption. An evaluation of the 4 years prior to, compared with the 4 years after, the introduction of the NIM in the US suggested that the programme effects an increased rate of adoption and, for those returned to birth families, a risk reduction of more than 50% in repeated maltreatment for both that child and subsequent siblings [34]. A follow-up of children several years after exposure to NIM in infancy has shown that on many mental health measures graduates of NIM, whether adopted or rehabilitated to birth families, differed only slightly from the general population [35]. These are apparently remarkable findings, when the high rates of psychopathology in populations of children in care are considered [36] but should be viewed with caution because these studies did not involve randomisation or control interventions and it is possible that other factors contributed to these outcomes. In particular, the Adoption and Safe Families Act, which placed tighter legal guidelines around judicial decision-making about young children in care, came into force just after the NIM service started in Louisiana [37] and it is quite possible that this could account for the improvement in children’s outcomes. In addition, the extent to which these findings could be generalised to a UK context is not known: in Louisiana, there is very little child welfare social work offered to families in the community [32] so NIM has never been tested against the Case Management that is routinely offered as part of UK social care.

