#### Primary outcome measure

Our primary outcome is child mental health, and our primary outcome measure is the Strengths and Difficulties Questionnaire (SDQ). This is a brief behavioural screening questionnaire for 2–16-year-olds (therefore always appropriate at time 3 even if the child entered the study near birth), completed by the primary caregiver (i.e. the caregiver with whom the child is living), with 25 items in 5 subscales: emotional symptoms, conduct problems, hyperactivity/inattention, peer relationship problems and prosocial behaviour [40]. It is sensitive to change in intervention studies, and effect sizes are moderate to large [41–43]. Our review of the literature suggests that SDQ is the most widely used and well-validated measure of mental health in children.

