## Statistical methods

### Statistical methods for primary and secondary outcomes {20a}

The primary analysis will use a generalised linear mixed effects regression model for the primary outcome measure to account for clustering of outcomes within families and adjusting for child age and other minimisation factors. The primary outcome measure is the Total Difficulties scale of the SDQ at 2.5 years after entering care. All models will be adjusted for age at the point of completion.

A single model over all three time points will be fitted. Interaction terms will be used to assess whether intervention effects vary between subgroups. The level of significance for the primary outcome is 0.05. A detailed Statistical Analysis Plan will be prepared and approved prior to database lock and unblinding of intervention groups.

We are analysing the trial on an intention-to-treat basis. Families who re-enter the study will not be re-randomised and, if appropriate, will receive assessment and treatment by the team to which they were previously randomised.

Blinded data analyses will be carried out during the trial, to determine the most appropriate method of allowing for clustering of outcomes within families. All modelling decisions taken during blinded analyses will be documented and approved prior to database lock. If modifications to the analysis are required following database lock, these will be documented and justified within the final statistical results.

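### Later siblings join the trial un-randomised after a care entry that NIM aims to influence; nothing shown keeps them out of the primary model, and their 2.5-year clock is contradictory

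*Protocol article*

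**What the plan says.** Trial design {8} describes a "cluster randomised controlled superiority trial with an allocation ratio of 1:1", with the family as the randomised unit. If a further child of a participating family is later taken into care, Inclusion (under Eligibility criteria {10}) has parents and carers asked for consent to include that child, and "the new child will not be randomised, but will instead be allocated to the same arm of trial as their previous family members". The reasons given are contamination, a possibly conflicting ethos, and that "the aim of NIM is to help the parent(s) become more nurturing for both the current and any future children".

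Intervention description {11a} cites a US before/after evaluation that suggested, for children returned to birth families, "a risk reduction of more than 50% in repeated maltreatment for both that child and subsequent siblings".

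Statistical methods {20a} models children's outcomes with terms "to account for clustering of outcomes within families and adjusting for child age and other minimisation factors" and states "We are analysing the trial on an intention-to-treat basis". Section {20c} expects no removals from analysis. Who will be blinded {17a} says participants know their arm.

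Outcomes {12} sets the primary outcome at 2.5 years post-randomisation. Statistical methods {20a} sets it at 2.5 years after entering care. Primary outcome measure says the SDQ, which starts at age 2, is "therefore always appropriate at time 3 even if the child entered the study near birth".

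**The concern.** Randomisation protects a comparison of the children who were present when the family was allocated. A later sibling enters only if two things happen afterwards: the child is removed into care, and the birth parents, who know their arm, agree. NIM is intended to change parenting of future children, so the first step may be affected by treatment. The second may be affected by knowledge of treatment. If either differs by arm, the arms will contain different numbers or kinds of later children, and a difference in mean SDQ could arise without any effect on the children in care at randomisation.

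The second matter is when such a child is assessed. For children in care at randomisation the two stated clocks nearly coincide. In the definitive-trial sequence, randomisation precedes a baseline visit that Table 2 places 4–14 weeks after care entry. For a later sibling the two clocks can be far apart.

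**Working it through.** **Analysis population.** Inclusion is a rule for entering the trial, not only for delivering a service. Sections {20a} and {20c} restrict the analysis neither to children present at randomisation nor to randomised children. The article does identify the narrower group: Sequence generation {16a} and the subgroup list in {20b} both use the children coming into care when the family is randomised. It does not use that group to define the primary analysis.

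**Benchmark.** The article gives no effect size, SD or ICC, so the 396-family target cannot be rebuilt from first principles. What follows from it is:

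- Evaluable families: 396 × 0.70 = 277.
- Consistency with the initial target: the ratio of required sizes at 90% and 80% power (two-sided 0.05) is 1.3387. Then 277.2 × 1.3387 gives 372 after rounding up, and 372 / 0.75 = 496 against the stated 492. The two targets agree if the printed 75% is read as retention.
- Implied detectable difference, clustering ignored: (1.960 + 0.842) × √(4/277) = 0.34 SD. The implied standard error is √(4/277) = 0.12 SD.

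**Illustrative bias.** These inputs are assumptions, not figures from the article: 198 families per arm (396 / 2), 1.4 index children per family (198 × 1.4 = 277 per arm), *p* = 0.10 to 0.30 later children per services-as-usual family, half that rate under NIM, and later children differing from index children by *d* = 0.3 to 0.5 SD on the SDQ. Let *a* = 198*p* (services as usual) and *b* = *a*/2 (NIM). With no effect of NIM on index children:

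bias = *d* × [*a*/(277 + *a*) − *b*/(277 + *b*)]

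| *p* | *a* | *b* | difference in shares | bias, *d* = 0.3 | bias, *d* = 0.5 |
|---|---|---|---|---|---|
| 0.10 | 19.8 | 9.9 | 0.0667 − 0.0345 = 0.032 | 0.010 SD | 0.016 SD |
| 0.30 | 59.4 | 29.7 | 0.1766 − 0.0968 = 0.080 | 0.024 SD | 0.040 SD |

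This is about 3% to 12% of 0.34 SD. Two-sided type I error rises from 5% to between about 5.1% and 6.3%. A wider grid (*p* 0.05–0.30, *d* 0.25–0.75, 1.0–1.4 index children per family) gives 0.004 to 0.075 SD, with type I error at most about 9.6%. If *d* = 0, or if later children are equally frequent and alike in the two arms, the bias is zero.

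**Time origin.**

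- *Clock of Outcomes {12}, using the family's randomisation date.* The final visit is at 30 months. A child born more than 30 − 24 = 6 months after randomisation is then under 24 months, below the SDQ's lower age limit. This contradicts the statement in Primary outcome measure.
- *Clock of Statistical methods {20a}, entry into care.* Every child is at least 2.5 years old, so the SDQ is age-appropriate. However, Table 1 ends the study on 29.02.2024, so a child entering care after about the end of August 2021 could not reach 2.5 years.
- *Table 2* uses both clocks: Visits 3 and 4 from care entry, Visit 5 from randomisation.

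**The case against.** The strongest reply is that the article never says later siblings enter the primary model. Inclusion governs enrolment and allocation. Analysis sets are commonly defined in a SAP, which {20a} promises before database lock and unblinding, and the index children are already identifiable. This stands in part: entry into the primary model is an inference from enrolment, intention to treat and the lack of any restriction. The enrolment rule itself, and the two conflicting clocks, are in the text.

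The same-arm rule is also defensible. The family is the randomised unit, and giving one family two approaches would invite contamination. That is accepted.

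A reader might infer that the plan itself expects NIM to halve later care entries. It does not. The figure in {11a} is limited to children returned to birth families, comes from a non-randomised comparison, and is followed by explicit cautions about a concurrent law change and UK generalisability. It shows the intended mechanism, not a rate for this trial.

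A reader might also infer that the SDQ simply fails for later siblings. That holds only on the randomisation clock, not on the care-entry clock.

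Finally, the calculation is generous. It assumes every later child is consented, uses a pooled mean although {20a} specifies a family-level mixed model, and ignores the adjustment for age at completion. These points would probably shrink the bias but would not remove it.

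**Conclusion.** The concern holds in a limited form. The article admits children to the trial un-randomised, on a post-allocation event that NIM aims to influence and after consent by parents who know their arm, and nothing shown confines the primary model to children in care at randomisation. If later siblings are included, the comparison is open to selection bias of about 0.01 to 0.04 SD under the assumptions above. Those assumptions (number of later children, a halving under NIM, and the SDQ shift) are not in the article.

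The documents do not support saying that the primary result will be biased, or biased towards NIM. Fewer removals under NIM could leave a milder or a more severe group of later children. The time origin is a plain contradiction between Outcomes {12} and Statistical methods {20a}, and it matters most for these children. The point is worth correcting because the remedy is cheap, not because the likely bias is large.

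**What to change.** - Keep the same-arm rule for service delivery.
- Define the primary analysis set as children in care at the family's randomisation, the group already used in {16a} and {20b}.
- Include later siblings only in a sensitivity analysis, with a stated time origin and only where follow-up allows.
- Report the number of later care entries by arm descriptively.
- Reconcile the time point in Outcomes {12} with that in Statistical methods {20a}, and bring the SDQ age statement into line with the choice.

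The cost is wording in the protocol and SAP and slightly fewer children in the primary model. No randomised family is lost, the 396-family target is unchanged, and this source of bias is removed from the primary comparison.
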